# Protocol for a randomized controlled trial of an internet-based prevention intervention for young children at-risk for functional abdominal pain

**DOI:** 10.1186/s13063-024-08371-8

**Published:** 2024-08-19

**Keywords:** Irritable bowel syndrome, Pediatric, Abdominal pain, Child, Parent, Prevention intervention, Internet interventions, Psychosocial intervention, Social learning, Cognitive behavioral therapy, Risk factors, Illness behavior, Solicitous behavior, Protective factors

## Abstract

**Background:**

Chronic pain often clusters in families, where parents and their offspring both experience chronic pain conditions. Young children of parents with irritable bowel syndrome (IBS) represent an at-risk group for the development of abdominal pain, disability, and excess health care visits in later childhood. Parental solicitous responses to children’s expressions of discomfort and maternal modeling of their own illness behavior contribute to a greater focus on somatic sensations, leading to illness behaviors in children. This randomized controlled trial will test the effectiveness of an early preventive web-based psychosocial intervention (REACH)[TM] vs. an educational web-based safety comparison condition delivered to parents with IBS to alter parental responses and lead to improved child health and decreased health care costs.

**Methods:**

Parents with IBS who have children ages 4–7 years are recruited via community-based approaches (e.g., social media advertisements, school electronic distribution, research networks) and health care providers. The target sample is 460 parents randomized to REACH, a web-based social learning and cognitive behavior therapy (SLCBT) intervention or an educational web-based safety comparison condition (EC). Participants will be assessed at baseline, 6-week (immediate post-intervention), 6-month, 12-month, and 18-month follow-up periods (months post-completion of intervention). The primary outcome is change in parental solicitous/protective behaviors. Secondary outcomes include parent risk and protective factors, child health and symptom outcomes, and health care utilization and cost savings.

**Discussion:**

This study adapts a validated, parent-delivered intervention to treat chronic pain in children to a web-based application designed to prevent the development of chronic pain in very young, high-risk children. If successful, this strategy can both prevent adverse sequelae of this condition from developing as well as be widely accessible. Furthermore, the availability of a prevention model for parent training could result in significant short- and long-term health benefits across a broad spectrum of conditions.

**Trial registration:**

ClinicalTrials.gov NCT05730491. Registered on February 15, 2023.

**Supplementary Information:**

The online version contains supplementary material available at 10.1186/s13063-024-08371-8.

## Introduction

### Background and rationale {6a}

How people perceive and react to somatic sensations, both acute and chronic, has sometimes been described as “illness behavior” [1]. Inappropriate illness behavior may include over and underreacting to somatic sensations, worrying, focusing, and reacting to somatic sensations. Misinterpretation of normal somatic sensations as symptoms of disease may also result in seeking unnecessary medical treatment (for oneself or one’s child) for minor complaints. In the case of children, inappropriate parental concerns about children’s expressions of discomfort may also contribute to an apparent worsening of symptoms and increased disability [2].

Unexplained symptoms and associated illness behavior in children are prevalent, disabling, and costly. Abdominal pain, the second most common recurrent pain complaint of childhood (after headaches), affects approximately 13.5% of children worldwide [3]. Frequent pain is associated with increased school absenteeism and missed work by parents [3, 4]. The majority of children with persistent abdominal pain meet criteria for functional abdominal pain disorder (FAPD), defined as episodic or continuous abdominal pain without evidence of an inflammatory, anatomic, metabolic, or neoplastic process that could explain symptoms [5]. FAPD is associated with significant illness behavior such as disruption of activity and high health care utilization, resulting in low health-related quality of life (HRQOL), as well as emotional distress in both children and parents [4, 6–14].

Familial clustering of idiopathic chronic abdominal pain has been observed [15]. Lewis et al. found that children whose mothers have a history of IBS are 62% more likely to report symptoms of gastrointestinal disease in the absence of physiological findings than those without IBS [16]. Walker and Greene [17] found a significant positive association between severity of somatic symptoms in children diagnosed with FAPD and similar symptoms in both mothers and fathers, suggesting that either parent may influence the development or maintenance of these symptom reports. A study by [name] et al. that examined idiopathic chronic abdominal pain rates between monozygotic and dizygotic twins and their parents concluded that the contribution of learning processes appeared to be greater than that of genetics in the development of idiopathic chronic abdominal pain [18].

There is mounting evidence that multiple factors, including parental modeling, solicitous responses, and beliefs, account for the development and maintenance of symptom reports in children with a diagnosis of FAPD [19–24]. Learning theory [25, 26] provides a strongly supported explanatory model for why gastrointestinal complaints may run in families. Children may learn from their parents by observing how parents react to their own illness symptoms (modeling) and/or by how parents respond to the children’s gastrointestinal symptoms (concern and reinforcement). Several randomized controlled trials (RCTs) have demonstrated the effectiveness of social learning theory approaches including parent cognitive behavioral interventions (such as parental reinforcement of wellness behaviors) for children with established chronic pain conditions, including FAPD [27–30]. Therefore, psychosocial interventions have become part of the recommended treatment for FAPD [31].

There is evidence that children may incur a significant increase in the risk for developing abdominal pain and disability just prior to, or in the first years of school [16, 32], suggesting that strategies to prevent illness behaviors should be implemented before they develop or are well established. However, to date, preventive interventions have not been used to target the illness behavior patterns in childhood that are critical precursors leading to development of FAPD. Developing strategies to prevent and/or reduce illness behavior in children at risk for FAPD has the potential to mitigate deleterious effects on children’s academic, social, and emotional development [33]. Prevention studies following participants as far as late adolescence or young adulthood have demonstrated positive, long-term effects on a range of developmental outcomes from interventions that targeted parenting skills and other external or internal risk factors during early childhood [34–36].

A social learning approach, with its emphasis on parent education and skills training, provides a potentially powerful framework for early intervention with families whose children are at higher risk for illness behavior due to their parent’s IBS or idiopathic abdominal pain. Intervening early, before patterns have a chance to become established, could truncate the development of illness behaviors (e.g., somatic complaints and activity avoidance) that often lead to disability. Intervening early can also improve children’s health-related quality of life and reduce children’s healthcare utilization, especially attributable to FAPD [37]. Though beyond the scope of this study, more distal goals of early, preventative intervention include forestalling the development of FAPD, with its potentially lifelong negative effects on health and well-being. Furthermore, delivering the intervention via the internet through approaches our team has successfully used with other CBT pain interventions enhances the potential for scalability and dissemination [38, 39].

Figure 1 provides the conceptual model of the targets and outcomes of the prevention intervention on which this study is based.

**Fig. 1 Fig1:**
[figure not shown]
Intervention targets and outcomes

Specifically, the intervention being tested here is designed to decrease risk factors for children of parents with IBS or idiopathic abdominal pain (parent catastrophic thinking about their own and their child’s symptoms and anxiety, and parenting stress) and increase protective factors (positive affect and social support). This, in turn, is expected to decrease parental solicitousness (primary outcome) as well as decrease children’s abdominal symptom complaints, and increase children’s physical, psychological, social, and school functioning, which will result in reduced health care utilization, and related direct and indirect costs including parent missed work time and costs of medical visits.

### Objectives {7}

This randomized controlled trial (RCT) aims to determine the efficacy of REACH (REsilient Active CHildren; https//reachkids.info), a web-based preventive social learning and cognitive behavior therapy (SLCBT) intervention delivered to parents with IBS, compared to an educational web-based safety comparison condition (EC) (aim 1). This trial also aims to determine the contribution of changes in parental risk and protective factors in mediating treatment effects (aim 2). Finally, we aim to determine cost savings of implementing this preventive intervention on health care expenditures and resource utilization over 18 months (aim 3).

The following hypotheses will be tested: (1) Parents receiving SLCBT will show lower solicitous behaviors (primary outcome) and lower levels of risk factors, including anxiety, parenting stress, and catastrophizing, than those receiving EC; (2) Parents receiving SLCBT will show increased levels of protective factors, including higher positive affect and social support, than those receiving EC; (3) Children of parents trained in SLCBT will have better physical, psychological, social, and school functioning, and fewer abdominal symptoms than those of parents in EC; (4) Changes in parental risk and protective factors will mediate treatment effects on child health-related quality of life; and (5) The SLCBT group will demonstrate superiority in a cost savings analysis compared to the EC group.

### Trial design {8}

This study utilizes a RCT with parallel 1:1 assignment to two study arms, (1) REACH, a SLCBT prevention intervention, and (2) an educational comparison condition (EC). Figure 2 provides the study recruitment flow and condition allocation.

**Fig. 2 Fig2:**
[figure not shown]
Study recruitment and measurement flowchart

## Methods: participants, interventions, and outcomes

### Study setting {9}

The study team is based at academic institutions and hospitals (University of Washington, Seattle Children’s Hospital, University of North Carolina at Chapel Hill, Cape Fear Valley Medical Center). Study participants, however, are recruited through social media outlets, newsletters, and relevant community groups (as described in Sect. 15) and may reside anywhere in the United States (because the intervention is web-based there are no limitations on participant location within the US). All participant data will be collected electronically through REDCap (Research Electronic Data Capture) [40], hosted at the University of Washington in Seattle, WA, USA.

### Eligibility criteria {10}

The study sample will include 460 parents with IBS who have young children ages 4–7 years. Complete inclusion and exclusion criteria are presented in Table 1.

**Table 1 Tab1:** Eligibility Criteria

**Inclusion criteria**
•The family has at least one parent (including biological or step-parent) who a) has been diagnosed with IBS or idiopathic abdominal pain in the last five years OR meets the ROME IV criteria [41] for IBS (abdominal pain at least weekly; pain related to defecation, change in stool frequency, and change in stool form at least 30% of the time), b) is the parent primarily responsible for caring for the child on a day-to-day basis (primary caregiver), and c) is willing to participate in the study. •The child is 4 to 7 years old at the time of screening. If multiple children in this age range are present in the family, the parent will be asked to select one child for study participation. •The child must currently live at least half of the time with the parent involved in intervention, in the U.S.
**Exclusion Criteria**
•The parent is not able to read, speak, and understand English. •The child has a developmental disability that requires full-time special education, as there may be differences in these families that influence intervention response compared to typically developing populations. •The child has daily chronic pain (pain most/every day for at least 3 months). •The child has a current doctor’s diagnosis of a painful gastrointestinal disorder like functional constipation, lactose/fructose/gluten intolerance, celiac disease, Inflammatory Bowel Disorder, etc. This does not include non-painful disorders like GERD. •The child has a severe chronic disease such as juvenile arthritis, cancer, or other severe condition(s) requiring chronic medical treatment. •The parent does not have regular access to the Internet on a desktop, tablet, smartphone, or laptop computer.

### Who will take informed consent? {26a}

If families are interested and eligible to participate, study staff will complete screening and obtain consent from parents and assent from participating children ages 7 or older via online REDCap e-consent forms.

### Additional consent provisions for collection and use of participant data and biological specimens {26b}

N/A: This study does not collect biological specimens, nor is it affiliated with any ancillary studies.

### Interventions

#### Explanation for the choice of comparators {6b}

This study has two intervention groups: education control (EC) and social learning and cognitive behavioral therapy (SLCBT) (see Sect. 11a below). As this study is novel, in that preventive interventions have not previously been applied to reduce intergenerational transmission of pain conditions, there is no standard for control conditions for prevention studies of this nature. Our team, however, has developed and tested SLCBT interventions in prior studies to change parental behaviors and modeling to reduce children’s illness behaviors; the education control comparator condition in this study is similar to those we have implemented in these prior large randomized controlled trials in children with FAPD and other pain conditions. The purpose of this comparator condition is to control for time, attention, and online usage, and to allow masking to treatment allocation.

#### Intervention description {11a}

##### Education control (EC) condition

Participants assigned to the control group will receive access to a web program and complete three modules focused on child health and safety behaviors, including sports and water safety, home and fire safety, and technology safety. The EC condition is designed to be completed in a 4-week period and uses several interactive elements to increase engagement including brief questions to assess participant knowledge, question/answer components, and instructional videos. The control condition is designed to match the active intervention in time, attention, and expectancy, three major components of the placebo effect. In two previous studies, a safety focused control condition produced credible treatment expectancy effects [42, 43].

##### Social learning and cognitive behavioral therapy (SLCBT) condition

Participants assigned to the SLCBT group will complete a 4-week web-based intervention. The website includes an introductory module, three skills-training modules (i.e., strategies to promote wellness behaviors, use adaptive cognitive coping, model wellness behaviors for their children, and determine when it is appropriate to take further action regarding potential illness in their child), and a brief maintenance and summary module. The web modules were designed to be visually attractive and interactive in order to engage participants through using brief questions to assess participant knowledge, interactive question/answer components, instructional videos, and storyboards that participants can click through. Screenshots can be seen in Fig. 3. Additionally, participants are provided a “Toolbox” in which informational handouts can be accessed, downloaded, and printed. The handouts provide a summary of the knowledge provided in each module. Participants in each group are instructed to log in to the website for 3–4 weeks, approximately 20–30 min per week. Research team members will regularly assess web program usage for all participants and will send reminders up to two times each week as needed to encourage regular usage and completion of all modules.

**Fig. 3 Fig3:**

Sample screenshots of REACH intervention conditions

### Criteria for discontinuing or modifying allocated interventions {11b}

This protocol is for a web-based prevention intervention, and as such, the intervention is not able to be modified. Participants may, however, opt out of the study at any time. There are no criteria for discontinuing intervention.

### Strategies to improve adherence to interventions {11c}

Adherence during the treatment phase is monitored as follows: Participants will receive a link to the study website via email. Participants will have the ability to log in and out of their online study dashboard as needed; when they log back into the website it will take them to the location where they left off. The study website will track participant progress and send reminder emails to complete each module if they are not completed within the module timeframe. Study staff will also track progress and send additional reminders to participants as needed to promote website usage. Once a participant has completed a module, they will receive another email informing them when their next module is ready to begin with a link to access their online study dashboard. These email contacts will ensure that accessing the study materials is convenient and efficient.

### Relevant concomitant care permitted or prohibited during the trial {11d}

Study participants are not prohibited from seeking other interventions or treatment during their participation in the study. Participants and their child(ren) can engage in any interventions (e.g., counseling, medication) as recommended by their care providers. The study team will collect information on any medical or psychosocial treatment received by the participants throughout their duration in the study.

### Provisions for post-trial care {30}

Adverse events are not expected, however, if they occur they are expected to be minor. Therefore, there are no provisions for any additional post-trial care or to provide compensation to those who suffer harm from trial participation.

### Outcomes {12}

The primary outcome is change in parental solicitous/protective behaviors. Secondary outcomes include parent risk and protective factors and child health and symptom outcomes. Participant outcomes will be assessed at baseline, immediate post-intervention (6 weeks) and at 6-month, 12-month, and 18-month follow-up periods. See also Sects. 6a and 18a.

### Participant timeline {13}

See Fig. 4.

**Fig. 4 Fig4:**
[figure not shown]
Schedule of enrollment, interventions, and assessments [13]. *-t_1_: enrollment timepoint; t_1_: pre-treatment timepoint. **t_2_–t_5_: post-intervention assessments (time 2 to time 5). ***Specific measures and timepoints are shown in Table 1

### Sample size {14}

Based on our prior studies with the intervention [43], we expect the intervention effect sizes for our primary outcome measure in the range of 0.30–0.40 (Cohen’s *d*). Using Optimal Design software [44], we calculated that a sample size of 210–380 families is sufficient to detect the expected effect sizes with a power of 0.80 and alpha = 0.05. Power to detect mediation in analyses was calculated using Monte Carlo estimation methods. For single mediator models such as those proposed here, a sample size of 368 has > 0.80 power to detect a medium sized indirect effect that explains 13% of the variance in the outcome.

### Recruitment {15}

Recruitment will be conducted through community-based approaches including health care providers, social media (e.g., postings with relevant groups and communities via Facebook, Twitter, Instagram, and others), school electronic distribution lists, and networks that connect volunteers with research projects (e.g., ResearchMatch). Potential participants complete a study interest and pre-screening form hosted on REDCap, a secure web-based data collection platform. Alternatively, they can contact study staff via a phone number or email provided in the study advertisement or through the study interest form, which provides complete details and easy links to assist in completion. A second wave of screening is conducted with interested parents wherein study staff contacts potentially eligible participants via phone call/voicemail, email, or text to see if the family is interested in hearing more about the study and assess eligibility.

### Assignment of interventions: allocation

#### Sequence generation {16a}

Group allocation will be determined using a computer-generated algorithm [45, 46] with equal assignments to each study arm, using randomly selected block sizes stratified by self-reported parent sex at birth.

#### Concealment mechanism {16b}

Allocation concealment will be ensured, as randomization does not occur until after baseline measurements have been completed.

#### Implementation {16c}

As described in Sect. 16a, the allocation sequence is generated using a computer-generated algorithm. The study coordinator(s) will screen, consent, and enroll participants, administer baseline measures (via REDCap), and initiate randomization (via REDCap).

### Assignment of interventions: blinding

#### Who will be blinded {17a}

With the exception of study coordinators and statisticians (see 17b), all other study staff will be blinded to treatment assignment. Blinding will be made possible through restricting access to participants’ treatment assignments in the study database only to staff whose role is to assign participants to interventions, contact participants throughout the intervention phase, or analyze results by treatment group. Study participants will also be blinded to treatment assignment as both treatment arms are using the same web site platform with the same branding, however participants may deduce their treatment group based on the content they receive.

#### Procedure for unblinding if needed {17b}

Study coordinators and statisticians will not be blinded to the treatment assignment. In the unlikely event that an adverse event should occur, unblinding of other study staff can be conducted by the study coordinator who assigns participants to interventions.

### Data collection and management

#### Plans for assessment and collection of outcomes {18a}

All outcome measures will be completed online independently by study participants, reducing risk of bias.

#### Measures

A list of measures with descriptions and timing of assessments can be found in Table 2.

**Table 2 Tab2:** Measures by timepoint

Measure	Description	Source^a^	T1^a^	T2	T3	T4	T5
***Demographics and background measures***							
Demographics form	Demographic questionnaire to report on parent and child sex, gender, race, and ethnicity; family income; and parent education	P/C	X				
Medical history	Parent medical, psychiatric, and surgical history (including chronic conditions and chronic pain) and child medical diagnoses (including abdominal pain)	P/C	X	X	X	X	X
Irritable Bowel Syndrome Symptom Severity Scale (IBS-SSS) [47]	5-item measure which assesses parent severity and frequency of abdominal pain, bloating severity, dissatisfaction with bowel habits, and the impact of these symptoms on everyday activities	P/C	X	X	X	X	X
Daily Parenting Hassles Scale [48–50]	20-item scale that assesses parent burden in meeting the needs of their children and troublesome behavior of children. Subscales include challenging behavior and parenting tasks	P/C	X				

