***Treatment acceptability, satisfaction, and engagement***							
Treatment Evaluation Inventory—Short Form (TEI-SF) [65]	The TEI-SF is a 4-item measure that assesses treatment acceptability and satisfaction. 9 additional items are intended to collect feedback on the study website	P/C		X			
Treatment engagement (website)	Number of logins to the program, number of modules completed, and number of completed assignments will be measured from the admin backend of the website	N/A		X			

^a^*P/C* Parent/caregiver, *Ch *Child, *N/A *Not applicable

^a^T1*= *baseline, T2 = Post-intervention, 4-6 weeks after baseline; T3 = 6-month follow-up; T4 = 12-month follow-up,  T5 = 18-month follow-up

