#### Analyses by aims

Aim 1: Determine the efficacy of a preventive SLCBT intervention delivered to parents with IBS compared to a time and attention placebo/education condition (EC) at post-intervention, and at 6-, 12-, and 18-month follow-up periods. Analyses for this aim will use an intent-to-treat and dose–response approach. Intent-to-treat analyses will test associations between a dichotomous treatment assignment variable and primary (hypothesis 1) and secondary parent outcomes (hypothesis 2), as well as child health and symptom outcomes (hypothesis 3). Efficacy tests will be conducted using multilevel modeling (MLM) to maximize power and account for the longitudinal design with nesting of observations within person/family. In addition, the use of multilevel modeling allows estimation of intervention effects at a specific time point (intercept) and change over time in intervention effects (slope; time × intervention interaction). For example, to test hypothesis 1, we will estimate a series of MLMs testing the effect of the dichotomous intervention assignment variable on the level (intercept) of Adult Response to Children’s Symptoms (ARCS) scores at each time point by systematically re-centering the intercept (e.g., model 1: intercept at post treatment, model 2: intercept at 6 months, etc.). Next, we will test the association between intervention assignment and the slope of ARCS scores across time points (time × intervention interaction). Controls will include parent age and sex, as well as child sociodemographic characteristics and parent pre-treatment irritable bowel syndrome severity. Dose–response analyses also will use MLM as described above; however, the dichotomous treatment assignment variable will be replaced with a treatment engagement score (e.g., modules completed).

Aim 2: Determine the contribution of changes in parental risk and protective factors as mediating treatment effects. Hypothesis 4 states that changes in parental risk and protective factors will mediate treatment effects on child health-related quality of life. Following the procedures outlined by Muthen and colleagues [66], we will test whether and to what extent parent pain catastrophizing mediates the association between intervention group and parent solicitous responses to child symptoms. Similar models will test other mediators, as well as secondary parent and child outcomes.

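### Parenting stress is a stated outcome and target of the intervention, but Table 2 shows no measure of it after baseline, so the effect on it cannot be estimated

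*Protocol article*

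**What the plan says.** Four places in the protocol article bear on this.

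- **Background and rationale {6a}, text with Fig. 1.** The intervention "is designed to decrease risk factors for children of parents with IBS or idiopathic abdominal pain". The risk factors listed are "parent catastrophic thinking about their own and their child’s symptoms and anxiety, and parenting stress".
- **Objectives {7}.** Hypothesis 1 predicts "lower levels of risk factors, including anxiety, parenting stress, and catastrophizing, than those receiving EC". Hypothesis 4 adds: "Changes in parental risk and protective factors will mediate treatment effects on child health-related quality of life".
- **Outcomes {12}.** Parent risk and protective factors are secondary outcomes. Participant outcomes are to be assessed at baseline, at 6 weeks, and at 6, 12 and 18 months.
- **Measures, Table 2.** The Daily Parenting Hassles Scale is described as a "20-item scale that assesses parent burden in meeting the needs of their children and troublesome behavior of children". It stands in the demographics and background block, not the outcome and process block, and has one mark, at T1. The footnote makes T1 the baseline and continues: "T2 = Post-intervention, 4-6 weeks after baseline; T3 = 6-month follow-up; T4 = 12-month follow-up", with T5 at 18 months.

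Two further statements fix the consequence. Under Concealment mechanism {16b}, "randomization does not occur until after baseline measurements have been completed". Under Analyses by aims, catastrophizing is the worked example for mediation, followed by: "Similar models will test other mediators, as well as secondary parent and child outcomes".

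**The concern.** The hypotheses and the measurement schedule do not agree. The protocol predicts a difference between arms in parenting stress and lists it among the factors the intervention should lower. The schedule, however, collects nothing identified as parenting stress once parents have been randomized.

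This is not a detail that an article may leave to an analysis plan, because no analysis plan can recover data that were never collected. If it stays as it is, one named part of hypothesis 1 will go unreported, or another scale will be put in its place after the fact. The second course invites a charge of selective reporting.

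**Working it through.** No sample size, power or alpha figure enters this point, and the plan gives no figure to reproduce. The check sets each parent construct named in hypotheses 1 and 2 against the marks in Table 2.

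| Construct | Instrument in Table 2 | Baseline (T1) | Post-baseline (T2–T5) |
|---|---|---|---|
| Solicitous behavior (primary) | ARCS Protectiveness | yes | 4 of 4 |
| Anxiety | GAD-2 | yes | 4 of 4 |
| Catastrophizing | PCS short form | yes | 4 of 4 |
| Positive affect | PANAS | yes | 4 of 4 |
| Social support | MSPSS | yes | 4 of 4 |
| Parenting stress | none identified; closest is the Daily Parenting Hassles Scale | yes (Hassles Scale) | 0 of 4 |

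**Could another repeated measure serve?** The remaining repeated parent-level measures are PHQ-2 (depression), IBS-SSS (the parent's bowel symptoms) and medical history. GAD-2 covers anxiety, which hypothesis 1 names separately from parenting stress. PANAS covers general positive and negative affect. None is described as measuring parenting stress or burden.

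**Is the single mark an artefact of text extraction?** This is unlikely. The Hassles row has the same pattern as the one-time demographics form, while the IBS-SSS row beside it carries all five marks. The CSRI row keeps a gap at T2 alone, so blank cells survived.

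**Treatment effect.** For a post-baseline time t, the target is E[Y(t) | SLCBT] − E[Y(t) | EC], with t = T2, T3, T4 or T5. The planned multilevel models estimate this level difference at each time point and the time-by-intervention slope. For parenting stress, Y(t) is observed for no parent at any of the four times. Only Y(T1) exists. It precedes randomization, so its expected difference between arms is zero by design and carries no information on efficacy.

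**Mediation.** An indirect effect is a × b, where a is the effect of assignment on the post-baseline mediator and b is the effect of that mediator on the outcome. With no post-baseline mediator, neither a nor b can be estimated.

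**Imputation.** The methods listed under {20a} and {20c} borrow from parents in whom the variable was observed. Here it is missing for everyone after baseline, so there is nothing to borrow from.

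**The case against.** The strongest reply is that little of the trial is touched. Parenting stress is one secondary construct in an illustrative list. The primary outcome, the sample size, the randomization and the cost analysis do not depend on it, and the one mediator that Aim 2 names, catastrophizing, is measured at every assessment. This stands. A reader might infer that the main efficacy result or Aim 2 as a whole is compromised; the documents do not support that.

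Second, no sentence says that the Hassles Scale is the measure of parenting stress. Its place among the background measures fits a deliberate baseline descriptor. This also stands, so the protocol does not show that the scale was meant to be repeated. It does not remove the contradiction: if the scale is not the measure, parenting stress is not measured at all.

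Third, a reader might count parenting stress as one of a fixed set of named mediators. The protocol gives no such set. Hypothesis 4 speaks only of parental risk and protective factors, and the Aim 2 text names catastrophizing and then refers to other mediators. Including parenting stress is a reasonable reading, because it is listed as a risk factor, but it is a reading.

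Fourth, it is tempting to say that data are being lost with every month of recruitment. That follows only if the scale is the intended outcome measure and the published table matches what REDCap collects. The article establishes neither.

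**Conclusion.** The inconsistency is real and should be fixed, but it is limited in reach. Hypothesis 1, the conceptual model and Outcomes {12} treat parenting stress as something to be compared between arms after the intervention. Table 2 provides 0 of 4 post-baseline assessments identified with it. As written, the effect on parenting stress and any mediation through it cannot be estimated. The primary outcome and the other risk and protective factors named in hypotheses 1 and 2 are unaffected.

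The conclusion assumes that Table 2 is complete and correctly marked. It does not depend on the Hassles Scale being the intended instrument. Which element is wrong (the table mark, the choice of instrument or the wording of the hypothesis) cannot be settled from the article.

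**What to change.** Reconcile Objectives {7}, the conceptual model, Outcomes {12} and Table 2. One of three routes applies.

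1. **The T1-only mark is an error.** Correct Table 2 to show what REDCap collects. The cost is a table correction.
2. **Parenting stress stays an outcome and is not being collected.** Add the Hassles Scale at the remaining T2–T5 assessments for parents still in follow-up. The cost is an amendment and 20 more online items per assessment. The item counts in Table 2 put the repeated parent-completed battery at 5 (IBS-SSS) + 15 (ARCS) + 2 (GAD-2) + 2 (PHQ-2) + 3 (PROMIS) + 6 (PCS) + 20 (PANAS) + 12 (MSPSS) + 5 (ROME IV) + 15 (PedsQL) = 85 items, before medical history and CSRI. The addition is therefore about 20/85 = 24% per assessment, in a trial that gives drop-out as its first limitation. Visits already passed stay missing. Recruitment began in October 2023, so the analysis of this outcome would rest on fewer parents and should say so.
3. **The added burden is not wanted.** Remove parenting stress from hypothesis 1 and the conceptual model, and state that it is not tested as an outcome or a mediator. The cost is a wording change.
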